
### Outcome Measures

Outcome measures together with the assessment schedule are presented in Table 1. Note that all participants complete the same questionnaires (T1, T2, T3, and purpose-designed 3-item weekly evaluation and engagement survey) regardless of the arm they are allocated to.

**Table 1 table1:** Schedule of assessments and measures.

Measure	Baseline (T1, week 1)	Intervention (weeks 2-9)	Postintervention (T2, week 9)	Follow-up (T3, week 13)
Purpose designed #chatsafe online safety questionnaire	✓	N/A^a^	✓	✓
Patterns of Social Media Use Questionnaire (including 12 items to assess social media usage for the purposes of communicating about suicide and-self harm specifically)	✓	N/A	✓	✓
Perceived Internet-Self Efficacy Scale	✓	N/A	✓	✓
Willingness to Intervene Against Suicide Questionnaire	✓	N/A	✓	✓
Patient Health Questionnaire-9	✓	N/A	✓	✓
Purpose designed 7-items assessing exposure to, and personal experiences of, suicide and self-harm	✓	N/A	✓	✓
Purpose designed 9-item Weekly Evaluation and Engagement survey	N/A	✓	N/A	N/A
Purpose designed 1-item assessing participant reasons for withdrawal/noncomplete	✓	✓	✓	✓
Purpose designed 10-items assessing participants’ evaluations of the intervention content immediately postintervention	N/A	N/A	✓	N/A
Sexual Health Capacity Scale	✓	N/A	✓	✓
Self-Efficacy Protective Sexual Behaviours Scale	✓	N/A	✓	✓
Sexual Health Questionnaire	✓	N/A	✓	✓

^a^N/A: not applicable.

### Randomization and Treatment Allocation

Participants will be randomized to the intervention or the control group using block randomization with varying block sizes. The allocation ratio will be 1:1. The randomization schedule is computer generated by independent information technology personnel with guidance from the study statistician (MS). The schedule will then be implemented by a member of the study team (other than the statistician) into the REDCap database management software for allocating treatments to individual participants. Except for the study statistician, the study team members are not blinded to the treatment allocations. The study statistician will not have access to the randomization component of the database and will not be informed about the treatment allocations and will therefore remain blinded. As the study statistician will not be involved in any aspect of this study's operations other than data analysis, there are no circumstances we could foresee under which the study statistician would be required to be unblinded.

### Statistical Analysis

At baseline, state of residence, postcode, age, Aboriginal or Torres Strait Island status, gender identity, sexual orientation, primary language spoken at home, cultural background, and educational and occupational background will be reported using descriptive statistics and will be checked for imbalance between trial arms. The moderating effect of gender (male, female, trans, and gender diverse), age group (ie, 16-20 and 21-25 years), time spent on social media, psychological distress, and previous experience of suicide and self-harm will be considered in analyses as covariates.

Analyses will be performed on an intention-to-treat basis, where all individuals randomized will be included in the analysis by their allocated trial arm status regardless of whether they received all, part, or none of the intended treatments. For the primary analysis, we will use linear regression to estimate the difference in the mean changes between the intervention and control arms at T2 in the outcome safety when communicating online about suicide, as measured via the #chatsafe online safety questionnaire. This analysis will adjust for T1 scores. Multiple imputation will be used to address attrition bias, with 50 imputation samples generated using chained equations. We will conduct 2 sensitivity analyses. One sensitivity analysis will be undertaken using complete cases only (ie, repeating the primary analysis but only analyzing participants who have complete T1 and T2 data). The second sensitivity analysis will use multiple imputation and include the following potential moderating factors as covariates: gender (male, female, transgender, and gender diverse), age group (ie, 16-20 and 21-25 years), time spent on social media, psychological distress, and previous experience of suicide and self-harm.

The secondary outcomes at T2 and T3 will be analyzed based on the primary analysis and the 2 sensitivity analyses. We will use linear regression for continuous outcomes, logistic regression for binary outcomes, and negative binomial regression for counts.

Potential iatrogenic effects will be analyzed on a weekly basis and will serve as an interim analysis throughout the course of the study. If the weekly content is assessed as “very distressing” by more than 20% of participants per week, the safety monitoring committee (SMC) will be consulted, and the content may be withdrawn. The acceptability of each week’s content will be analyzed and reported as descriptive statistics (frequencies and percentages).

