### Participants and Recruitment

Participants will be 400 young people (200 per arm of the trial). Inclusion criteria are being aged between 16 and 25 years, living in Australia, having used social media to communicate about suicide or self-harm *or* having seen suicide- or self-harm–related information on social media, having not previously participated in a research study that was focused on evaluating suicide prevention or sexual health–related content on social media, considering oneself as being an active social media user, and being willing to share one’s mobile phone number with the research team so that one can be contacted with regard to trial-related communications.

Participants will be recruited via social media advertising using Orygen’s social media accounts. Young people who wish to participate will be directed to a brief self-assessment questionnaire to assess eligibility. They will then automatically be directed to a web-based consent form, which explains the key aspects of study involvement and consent process. This is followed by the T1 questionnaire, after which, participants will be randomly allocated to either the intervention group (#chatsafe intervention) or the control group.

The participant flowchart is shown in Figure 1.

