### Study Outcomes

The primary outcome is safety when communicating online about suicide, as measured via the purpose-designed #chatsafe online safety questionnaire at T2. This measure was specifically designed for this purpose by 3 study authors (JR, [name], and CC).

Secondary outcomes are (1) confidence when communicating on the internet about suicide, as measured via the purpose-designed #chatsafe online safety questionnaire at T2; (2) willingness to intervene against suicide on the internet, as measured via the Willingness to Intervene Questionnaire at T2 [15]; (3) internet self-efficacy, as measured by the Internet Self-Efficacy Questionnaire at T2 [16]; (4) safety of the weekly #chatsafe content, as measured by the purpose-built weekly evaluation and engagement survey; (5) acceptability of the #chatsafe intervention, as measured by the purpose-built T2 evaluation questions; and (6) safety of the #chatsafe social media intervention (as a whole), as measured by the number of (or absence of) adverse events recorded throughout the trial. Participant adverse events include (1) participant response to item 9 on the 9-item Patient Health Questionnaire [17] at baseline (time 1), time 2, or time 3. (2) Participant response to the 9-item weekly evaluation survey indicates distress, measured by participants selecting “very distressed” in response to the question “To what extent did you find the content this week distressing?” (3) Participant response to the T2 evaluation questionnaire indicates that a particular piece of campaign content made them feel distressed or at risk of suicide. (4) The participant directly contacts the research team via social media or email and reports distress or risk of harm to self. All adverse events will be responded to by the study team, in line with the study’s safety management strategy. (7) Feasibility of the #chatsafe social media intervention was measured by campaign reach via social media analytics, and participant retention or attrition via audit of study enrollment and withdrawal logs. (8) Self-reported evaluations of the acceptability of receiving the #chatsafe social media intervention were measured by purpose-designed study questions. Exploratory outcomes are as follows: (1) subgroup differences (gender, age, previous exposure to, previous experiences of suicide and self-harm, and level of social media usage) at T2 and (2) self-reported open-ended evaluations of the safety, feasibility, and acceptability of receiving the PROSPEct social media intervention for sexual health promotion in the control group at T2.

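### Age is cut into two bands (16-20, 21-25) without a stated reason, which weakens the exploratory age-moderation question if the effect of age is roughly linear; the primary analysis is unaffected

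*Protocol article*

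**What the plan says.** All references are to the protocol article.

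- **Age is recorded.** Statistical Analysis lists it among the baseline variables: "At baseline, state of residence, postcode, age, Aboriginal or Torres Strait Island status, gender identity". Neither unit nor precision is given. Eligibility bounds it: "Inclusion criteria are being aged between 16 and 25 years" (Participants and Recruitment).
- **Age is banded as a moderator.** The same section says that "age group (ie, 16-20 and 21-25 years), time spent on social media, psychological distress, and previous experience of suicide and self-harm will be considered in" the analyses as covariates.
- **Age is banded as a covariate.** "The second sensitivity analysis will use multiple imputation and include the following potential moderating factors as covariates", and the list that follows repeats the same two bands: "age group (ie, 16-20 and 21-25 years), time spent on social media". Both sensitivity analyses are carried over to the secondary outcomes at T2 and T3.
- **The primary model has no age term.** "This analysis will adjust for T1 scores" is the only adjustment named.
- **The subgroup question.** Aims and Hypotheses plans to examine differences between age groups. Study Outcomes lists, as exploratory, "subgroup differences (gender, age, previous exposure to, previous experiences of suicide and self-harm, and level of social media usage", without naming bands.
- **Randomization.** Varying blocks at 1:1, with no stratification by age stated.

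No section explains the boundary between 20 and 21.

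**The concern.** With two bands, a 16-year-old and a 20-year-old count as the same, and any effect of age is placed between 20 and 21. Because the bands are not stated to be a randomization factor, the design does not require them in the model. The article states this coding explicitly, so it is not a detail left to a fuller document.

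What is at stake is mainly power. Whether the intervention works differently by age is a declared question, and interaction tests start from a weak position in a trial sized for its primary outcome. A coding that discards recorded information weakens them further. A lesser question is whether leaving some variation by age unexplained matters for the adjusted treatment effect.

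**Working it through.** **What the article gives.** It contains no figure on the information lost by banding. Its only power statement is about 400 participants (200 per arm) at 5% significance and 80% power for the primary outcome, with no effect size or SD. That size cannot be reproduced. Solved backwards (two-sided, no attrition), it corresponds to d = (1.960 + 0.842) × √(2/200) = 0.28. Nothing in the article sizes an age interaction, so the 80% used below is a reference point, not a claim of the plan.

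**Step 1: information kept by the bands.** For a linear age effect, or a linear arm-by-age interaction, the efficiency of the bands relative to age in years is the squared correlation between age and the band indicator. Assume whole-year ages spread evenly over 16-25:

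- variance of age = (10² − 1)/12 = 8.25
- band means 18 and 23, so between-band variance = 2.5² = 6.25
- efficiency = 6.25/8.25 = 0.758, a loss of 24.2%

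With age continuous and uniform over ten years, the figure is 6.25/(100/12) = 0.750, a loss of 25.0%.

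**Step 2: other age distributions.** The article gives none, so these are assumptions.

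| Assumed distribution | Efficiency | Loss |
|---|---|---|
| U-shaped, weight proportional to distance from 20.5 | 0.889 | 11% |
| Geometric decline with age, ratio 0.8 | 0.712 | 29% |
| Linear decline (or rise) with age | 0.694 | 31% |
| Normal-shaped, centre 20.5, SD 2 | 0.669 | 33% |
| Geometric decline with age, ratio 0.7 | 0.643 | 36% |
| Normal-shaped, centre 19, SD 2.5 | 0.643 | 36% |
| Normal, split at its median (2/π) | 0.637 | 36% |

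**Step 3: power of a linear arm-by-age test.** Suppose 80% power on age in years, two-sided 5%. The expected test statistic is 1.960 + 0.842 = 2.802. On the bands it is multiplied by the square root of the efficiency:

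- even ages: 2.802 × √0.758 = 2.439; power = Φ(2.439 − 1.960) = 0.68. The equivalent sample size is 400 × 0.758 = 303.
- efficiency 0.889: Φ(2.802 × √0.889 − 1.960) = 0.75
- efficiency 0.637: Φ(2.802 × √0.637 − 1.960) = 0.61

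A simulation with N = 400, even ages and 4000 replicates gave 81% on age in years and 68% on the bands.

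**Step 4: the opposite shape.** The same simulation with moderation that changes in a step at 21 gave 68% on age in years and 79% on the bands. The ranking depends on the shape of the effect.

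**Step 5: the adjusted treatment effect.** If age has partial R² = R with the outcome, banding multiplies the standard error of the treatment effect by √[(1 − 0.758R)/(1 − R)]:

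- R = 0.01: √(0.9924/0.99) = 1.001, up 0.1%
- R = 0.05: up 0.6%
- R = 0.10: √(0.9242/0.90) = 1.013, up 1.3%

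The values of R are assumed; the article gives none.

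**The case against.** The strongest reply is that the bands answer the question asked. Aims and Hypotheses speaks of age groups, not of age in years. The bands are named in advance, span the whole eligible range in two sets of five whole years, can be read directly and need no assumption of linearity. If the effect steps at 21 they are the better coding. This stands, so a reader who infers that banding brings no benefit goes further than the article allows. It is also why the bands should be kept for the group comparison. It does not justify using them as the only coding: no section claims a step at 21 or explains that boundary.

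A second reply is that the loss of power concerns a test the article does not write out. It enters the moderators as covariates, and a main-effect covariate does not test moderation under either coding. That is a separate matter which recoding age would not cure, and the form of the interaction test may be left to a fuller document. The power figures therefore describe what an arm-by-age test would lose if it used the stated bands.

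A third reply is that little depends on it: one sensitivity analysis and exploratory work. This also stands and limits the weight of the point.

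A reader might also see a contradiction between age in Study Outcomes and age group in Statistical Analysis. The former reads naturally as shorthand in a list.

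**Conclusion.** The point holds as a minor improvement. The article fixes a two-band coding of a recorded variable, at an unexplained cut, for a question it says it will examine. The loss is about a quarter of the information on age if ages are evenly spread and the effect is linear, and about 11% to 36% under the other distributions tried. With even ages, 80% power for a linear interaction becomes about 68%.

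The quarter is conditional: the article gives neither an age distribution nor a shape for the effect, so it should not be read as an established loss. Nor do the documents support the inference that residual variation by age compromises the trial's results. Age is absent from the primary model, and in the adjusted model the standard error rises by about 0.1% to 1.3% for an assumed partial R² of 0.01 to 0.10.

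**What to change.** In Statistical Analysis, enter age in years, linearly or with a simple curved term fixed in advance, in the second sensitivity analysis and in the arm-by-age test. Keep 16-20 and 21-25 as the prespecified bands for the age-group comparison announced in Aims and Hypotheses, and add a sentence on why the boundary was chosen.

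The cost is wording only: no new data, provided age is held at least in whole years, and no change to the design or the primary analysis. The trade-off is that a functional form for age must be assumed, and power would be lower if the effect truly changed in a step at 21. Retaining the banded comparison partly covers that case.

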### Aims and Hypotheses

The overall aim of the study is to assess the impact of the #chatsafe social media intervention on young people’s safety and confidence when communicating on the internet about suicide. In this study, the treatment group who will receive the #chatsafe social media intervention will be compared to the control group who will receive social media content providing education on sexual health and well-being.

It is hypothesized that (1) At postintervention (T2), the treatment group will have higher mean scores than the control group on their understanding and compliance with the #chatsafe guidelines, as measured by the #chatsafe online safety questionnaire. Specifically, this will be assessed by improvements in their understanding of language to use or not use, support services available to them, how to share their own experiences of suicide safely, how to communicate about those who have died by suicide, and how to support someone that they are worried about. (2) At the postintervention time point (T2), the treatment group will have higher mean scores than the control group on self-reported (i) safety and confidence when communicating on the internet about suicide, (ii) willingness to intervene against suicide on the internet, and (iii) perceived internet self-efficacy. (3) It will be safe and acceptable to share the #chatsafe intervention with young people entirely via social media (assessed weekly throughout the intervention and postintervention [T2]). (4) Knowledge gains made in the intervention group at T2 will be maintained at T3.

Subgroup differences in perceptions toward the intervention and outcomes of the intervention (ie, gender, sexuality, age groups, and level of social media usage) will also be examined.

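### Moderators are entered only as covariates, which cannot show whether the effect on outcomes differs between subgroups

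*Protocol article*

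**What the plan says.** Three sections of the protocol article bear on this.

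- **Aims and Hypotheses**, after the four numbered hypotheses, adds a subgroup aim: "Subgroup differences in perceptions toward the intervention and outcomes of the intervention (ie, gender, sexuality, age groups, and level of social media usage".
- **Study Outcomes** lists as the first exploratory outcome "subgroup differences (gender, age, previous exposure to, previous experiences of suicide and self-harm, and level of social media usage) at T2".
- **Statistical Analysis** names the target as "The moderating effect of gender (male, female, trans, and gender diverse), age group (ie, 16-20 and 21-25 years), time spent on social media", and the same sentence ends with the method: "psychological distress, and previous experience of suicide and self-harm will be considered in analyses as covariates". It later says: "The second sensitivity analysis will use multiple imputation and include the following potential moderating factors as covariates", followed by the same five factors.

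The primary model is given separately: "we will use linear regression to estimate the difference in the mean changes between the intervention and control arms at T2", and "This analysis will adjust for T1 scores". Secondary outcomes at T2 and T3 follow the primary analysis and the two sensitivity analyses. The article mentions no arm-by-factor interaction and no subgroup-specific estimate.

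**The concern.** Moderation means that the difference between arms changes with the level of a factor. Adding the factor to the model as a covariate accounts for differences in score level between, say, younger and older participants, but still estimates one arm effect for everyone. Target and method are joined in a single sentence, and the method is repeated as a model specification. This is therefore a stated method that does not fit its stated purpose, and not a detail left open.

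At stake is the outcome part of the exploratory subgroup aim. An analyst who follows the text exactly has no estimate of effect modification to report. In addition, because the factor lists differ between sections, a reader cannot tell which subgroup comparisons were prespecified.

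**Working it through.** **The plan's own figure.** The article gives no figure for the subgroup analysis. Its only sample-size statement (Sample Size and Statistical Power) is about 400 participants, 200 per arm, at 5% significance and 80% power, with no effect size or SD. It cannot be reproduced forwards. Solved backwards, with a two-sided test assumed:

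detectable difference = (1.960 + 0.842) × √(2/200) = 0.280 SD.

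As a check, 200 per arm has 79.96% power at 0.28 SD.

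**What the stated model contains.** The second sensitivity analysis, as written, is

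T2 = a + b·arm + c·T1 + d·factor + error.

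The arm effect is b when factor = 0 and b when factor = 1, so the difference between subgroups is zero by construction. The coefficient d is a difference in score level, averaged over the arms. Adding e·(arm × factor) makes the arm effect b in one subgroup and b + e in the other; e is the moderation. For binary and count outcomes the same holds on the log-odds and log-rate scales.

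**Numerical illustration.** 3,000 simulated trials, 200 per arm, an evenly split binary factor, and an assumed T1-T2 correlation of 0.5:

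| Truth | Covariate model: arm effect | Covariate model: factor coefficient | Interaction model: interaction |
|---|---|---|---|
| Arm effect 0 in one subgroup and 0.56 SD in the other | 0.28 | 0.28 | 0.56, significant in 90% |
| Arm effect 0.28 SD in both; factor shifts scores by 0.5 SD | 0.28 | 0.50, significant in 100% | −0.002, significant in 4.9% |

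The covariate model gives the same arm effect in both rows, although only the first has any moderation. Its factor coefficient equals the interaction in neither row.

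**The factor lists side by side.**

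| Factor | Aims | Exploratory outcome | Statistical Analysis (moderators) |
|---|---|---|---|
| Gender | yes | yes | yes |
| Age | yes | yes | yes |
| Social media use | yes | yes | yes |
| Sexuality | yes | no | no (baseline descriptive only) |
| Past experience of suicide or self-harm | no | yes | yes |
| Past exposure | no | yes | not named separately |
| Psychological distress | no | no | yes |

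Table 1 measures exposure and personal experience with one 7-item instrument, so the past-exposure row may be a matter of shorthand. Sexuality and distress are clear mismatches.

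**Precision of the right contrast.** With N analysed, 1:1 allocation and a share p in one subgroup, in SD units:

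SE = √[(4/N)(1/p + 1/(1−p))]; detectable interaction = 2.802 × SE.

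For N = 400 without T1 adjustment (subgroup shares are assumptions):

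| Split | SE | Detectable interaction | Power for a 0.28 SD interaction |
|---|---|---|---|
| 50:50 | 0.200 | 0.56 SD | 29% |
| 30:70 | 0.218 | 0.61 SD | 25% |
| 10:90 | 0.333 | 0.93 SD | 13% |

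T1 adjustment multiplies the SE by √(1 − r²). For a 50:50 factor, r = 0.5 gives 0.560 × 0.866 = 0.49 SD and r = 0.7 gives 0.560 × 0.714 = 0.40 SD; both correlations are assumed. Attrition works the other way: if an assumed 80% are analysed, 0.560/√0.8 = 0.63 SD without T1 adjustment.

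**The case against.** The best defence is that this is a condensed article whose analysis plan is not shown. Interaction terms for an exploratory analysis are normally set out there, and the word covariates may be loose. That limits what can be claimed. A reader might infer that the subgroup aim will go unanswered or be answered wrongly; the article does not support that, because the analysis plan may specify interactions. It does not rescue the wording, since the article states a method instead of deferring it, and an analysis plan with interactions would depart from that text.

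Three further objections stand:

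- The aim is exploratory and lies outside the numbered hypotheses. The covariate-adjusted model is a legitimate sensitivity analysis of the main effect; only its label is wrong.
- The aim also covers perceptions of the intervention. Comparing how subgroups within the #chatsafe arm rate its content needs no interaction.
- A reader might infer that the covariate coefficients will be reported as differences in benefit. The simulation shows that this would mislead, but nothing in the article says the coefficients will be read that way.

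It is also tempting to attach a familywise error rate, or to carry the pilot's completion (189/507 = 37%) over to this trial. The sections list four, five and five factors, so no single count of tests is fixed. The pilot figure describes completion of all three time points in a 12-week programme, whereas the analysis here is at T2 after 8 weeks.

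**Conclusion.** The point holds within limits. As stated, the method cannot show whether the effect on outcomes differs by gender, age group, social media time, distress or past experience, so it does not address the outcome part of the exploratory subgroup aim. This follows from the form of the model and depends on no assumed number. Sexuality and psychological distress are listed inconsistently across the three sections. The primary comparison is not affected.

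The numbers describe what a suitable analysis could detect, not harm from the current text: about 0.56 SD for an even split with 400 analysed, or 0.40 to 0.49 SD under the assumed T1-T2 correlations, and more with attrition or uneven subgroups. That is about twice the 0.28 SD main effect implied by the sample size. All of them assume a two-sided 5% test and 80% power.

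**What to change.** - Describe the second sensitivity analysis as prognostic covariate adjustment of the main effect, and drop the moderation label from it.
- For the outcome part of the subgroup aim, add arm-by-factor interactions to the T2 model, using T1 values of the factors. Report the interaction and the within-subgroup arm effects with 95% confidence intervals.
- Use an imputation model compatible with those interactions, so that imputing without them does not pull the estimates towards no moderation.
- State one factor list and use it in Aims and Hypotheses, Study Outcomes and Statistical Analysis, settling whether sexuality, psychological distress and past exposure belong.
- Label these analyses exploratory and state their limited precision.

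The cost is a wording change and a few extra regressions, best fixed before the data are analysed. No new data are needed: the scales are scheduled at T1 in Table 1, and age, gender identity and sexual orientation are among the baseline variables in Statistical Analysis. The drawback is imprecision: a non-significant interaction would not show that the effect is the same in all subgroups.
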